## **c. Objectives**

The overall aims of this study are to assess the impact of a subset of the National Adherence Guidelines’ minimum package of interventions on HIV patients’ treatment outcomes at public sector clinics; estimate the costs of the interventions; and describe the cascade of care for TB, hypertension, and diabetes at these same clinics. All implementation of the interventions and generation of data will be done by NDOH; this protocol, which has been developed in partnership with the National Department of Health, is solely for the analysis of routinely collected data.

The specific objectives of the evaluation are to:

*Objective 1: Among HIV-infected patients newly eligible for antiretroviral therapy,* ***evaluate the impact of Fast Track Treatment Initiation Counselling on initiation and viral suppression****.*

Research questions:

- What is the effect of Fast Track Initiation Counselling on rates of initiating ART within 30 days of determining ART eligibility?
- What is the effect of Fast Track Initiation Counselling on rates of being alive, in care, and virally suppressed within 9 months of determining ART eligibility?

*Objective 2: Among HIV-infected patients who are stable on antiretroviral therapy,* ***evaluate the impact of Adherence Clubs on ART adherence and viral suppression****.*

Research questions:

- What is the effect of Adherence Clubs on medication possession over the first 3 months of intervention eligibility compared to standard of care?
- What is the effect of Adherence Clubs on rates of viral suppression within 12 months of intervention eligibility compared to standard of care?

*Objective 3: Among HIV-infected patients who are stable on antiretroviral therapy,* ***evaluate the impact of Decentralized Medication Delivery on ART adherence and viral suppression****.*

Research questions:

- What is the effect of Decentralized Medication Delivery on medication possession in the first 3 months after intervention eligibility compared to standard of care?
- What is the effect of Decentralized Medication Delivery on rates of viral suppression within 12 months of intervention eligibility compared to standard of care?

*Objective 4: Among HIV-infected patients who have poor adherence to antiretroviral therapy,* ***evaluate the impact of Enhanced Adherence Counselling on treatment adherence and viral suppression****.*

Research question:

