## **b. Adherence Clubs**

Adherence clubs comprise adherent and stable patients on ART who meet at facilities or identified locations in the community, in groups of up to 30 patients every two to three months to receive group counseling, have a clinical assessment, and receive the required supply of pre-packed medications. Adherence clubs are managed by lay staff at the health care facility with support from community health workers. The goal is to keep patients engaged in care and adherent to their medication by providing social support and facilitating medication delivery and treatment monitoring, while also reducing patient visit burden on the clinics[13]. The adherence guidelines SOP provides detailed instructions for establishing and running the clubs and for eligibility criteria and data collection.

| *Primary outcome:* | Proportion of patients eligible for participation in an adherence club who receive all medications within the first 4 months after eligibility |
| --- | --- |
| *Eligibility:* | All adult patients who meet the criteria for being stable on ART (on same ART treatment regimen for at least 12 months; most recent viral load taken in past 6 months, 2 consecutive viral loads undetectable ) OR where a clinician confirms eligibility as a stable patient |
| *Sample size:* | 576 (288 per arm; 24 per cluster) |
| *Data sources:* | Tier.Net; pharmacy records; club register; other registers or records that document services provided during the period of club observation |

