## **c. Decentralized Medication Delivery**

Decentralized medication delivery through the “Centralized Chronic Medication Dispensing Distribution” (CCMDD) uses locations other than the clinic pharmacy to deliver medications to patients who are stable on treatment. Patients then only need to come to the clinic on a six monthly basis for a clinical exam. The goal is to reduce the burden on the patient in terms of the time and resources it takes them to collect their medication to improve treatment adherence and retention in care, while also decongesting the clinics.

| *Primary outcome:* | Proportion of patients eligible for decentralized medication delivery who receive all medications within the first 3 months after eligibility |
| --- | --- |
| *Eligibility:* | All adult patients who meet the criteria for being stable on ART (on same ART treatment regimen for at least 12 months; most recent viral load taken in past 6 months, 2 consecutive viral loads undetectable ) OR where a clinician confirms eligibility as a stable patient |
| *Sample size:* | 576 (288 per arm; 24 per cluster) |
| *Data sources:* | Tier.Net; pharmacy records; pickup point records or CCMDD registers or databases; other registers or records that document services provided during period of decentralized delivery |

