**Table 3. Evaluation outcomes**

| **Objective** | **Primary Outcome** | **Secondary outcomes** |
| --- | --- | --- |
| Fast track ART initiation counseling (Objective 1) | Proportion of patients who initiate ART within 30 days of becoming ART eligible (S) and the proportion of patients who are alive, in care, and virally suppressed (< 400 copies/ml^3^) within nine months of ART eligibility (L). | Proportion of patients who initiate ART within one week of becoming ART eligible  Demographic and clinical characteristics of patients who do and do not achieve primary outcomes (age, sex, baseline CD4 counts, TB diagnosis, other characteristics as allowed by data). |
| Adherence clubs (Objective 2) | Proportion of patients eligible for participation in an adherence club who receive all medications within the first four months after club eligibility (S) and the proportion virally suppressed (< 400 copies/ml^3^) at twelve months after club eligibility (L). | Proportion of patients consistently participating in club  Demographic and clinical characteristics of patients who do and do not achieve primary outcomes. |
| Decentralized medication delivery (Objective 3) | Proportion of patients eligible for decentralized medication delivery who receive all medications within the first three (S) months after delivery eligibility and viral suppression (< 400 copies/ml^3^) twelve months after delivery eligibility (L). | Proportion of patients consistently receiving medications  Demographic and clinical characteristics of patients who do and do not achieve primary outcomes. |
| Enhanced adherence counseling (Objective 4) | Proportion of patients with an elevated viral load who are alive, retained in care and resuppress their viral load (< 400copies/ml^3^) within three (S) and twelve months (L) of eligibility for enhanced adherence counseling. | Demographic and clinical characteristics of patients who do and do not achieve primary outcomes. |
| Early tracing of patients lost to follow up (Objective 5) | Proportion of patients eligible for early patient tracing who return to care within three (S) and twelve (L) months of eligibility. | Proportion of patients reached by tracers  Number of tracing attempts required; proportion of patients retained in care for at least one additional routine visit after tracing  Demographic and clinical characteristics of patients who do and do not achieve primary outcomes. |

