## **b. Sample Size**

Table 4 shows the sample size that is required to detect meaningful differences for Objectives 1-5 and for estimating precise rates for Objective 8. Each sample size is determined to measure our short term outcome for the objective. For Objectives 1-5, all calculations assume a site-clustered design with the clinic as the cluster; 24 clusters evenly split (randomized) between intervention and comparison groups; a coefficient of variation of 0.1, 80% power; and an alpha of 0.05.

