**Table 4. Sample sizes for each objective**

| **Objective** | **Sample Size** | **Rationale** |
| --- | --- | --- |
| Objective 1—Fast Track ART Initiation Counseling | 720 patients | The RapIT study of rapid ART initiation, conducted at a well-managed PHC in Gauteng Province, found that about 60% of ART-eligible patients initiated under standard care within 30 days. Conservatively assuming 60% initiation without the intervention and 75% with the intervention, 30 subjects in each of the 24 clusters for 720 total subjects will be required to detect a difference of 15%. We have increased this by 20% to account for ineligible patients. |
| Objective 2—Adherence Clubs | 576 patients | Data from Themba Lethu Clinic show that about 80% of patients made all of their medication pickups over a three month period. It is anticipated that 24 subjects per clinic for a total of 576 patients will be needed to detect a difference of 15%. We have increased this by 20% to account for ineligible patients. |
| Objective 3—Decentralized Medication Delivery | 576 patients | Data from Themba Lethu Clinic show about 80% of patients made all of their medication pickups over a three month period. It is anticipated that 24 subjects per clinic for a total of 576 patients will be needed to detect a difference of 15%. We have increased this by 20% to account for ineligible patients. |
| Objective 4—Enhanced Adherence Counseling | 1008 patients | Data from KZN indicate that 52% of patients with a detectable viral load re-suppress after one session. It is anticipated that 42 subjects per clinic for a total of 1008 patients will be needed to detect a difference of 15%. We have increased this by 20% to account for ineligible patients. |
| Objective 5—Early tracing of patients lost to follow up | 576 patients | Data from various Right to Care clinics suggest that the proportion of patients who are lost from care who return with no or little intervention is low, between 20-35%. It is anticipated that 24 subjects per clinic for a total of 576 patients will be needed to detect a difference of 15% assuming a baseline of 30% loss to follow up without intervention. We have increased this by 20% to account for ineligible patients. |
| Objective 6—overall impact | 0 patients | No additional subjects will be enrolled for the overall impact analysis, which will rely on data from Cohorts 1-5. |

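### The adherence-club short-term primary outcome has two windows and three descriptions of the measure, and if it is scored as pickups kept it depends on the dispensing schedule

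*Protocol*

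**What the plan says.** The outcome definition in section 4.b is "Proportion of patients eligible for participation in an adherence club who receive all medications within the first 4 months after eligibility". Table 3 gives the same four-month window and marks it as the short-term primary outcome.

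The matching research question in section 3.c is "What is the effect of Adherence Clubs on medication possession over the first 3 months of intervention eligibility compared to standard of care".

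Section 10.b states: "Each sample size is determined to measure our short term outcome for the objective". The Table 4 entry for Objective 2 then takes its control rate from a clinic where "about 80% of patients made all of their medication pickups over a three month period", and plans to detect a difference of 15%.

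On schedules, section 4.b says that clubs meet "in groups of up to 30 patients every two to three months" and that members receive their medication there. The protocol does not state the pickup interval under standard care. For decentralized delivery (Objective 3), the outcome is patients "who receive all medications within the first 3 months after eligibility". Section 4.c gives a six-monthly clinical exam but no medication pickup interval.

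**The concern.** Two problems meet in one primary outcome.

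First, the protocol fixes the window twice, differently, and describes the quantity in three ways: possession, receipt of all medications, and attendance at all pickups. These can disagree for the same patient. Someone who misses one scheduled pickup may still have medication in hand. The ambiguity carries forward, because Table 3 builds the Objective 6 primary outcome on the short-term outcomes and includes a cost per primary outcome achieved under Objective 7.

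Second, only one of the three descriptions has a planning rate, namely all pickups made. That is an all-or-none count, so a patient with fewer pickups due meets it more easily at the same level of adherence. Clubs may change the number due. Randomizing clinics does not remove this, because the schedule is part of the intervention. At stake is whether a club benefit on this outcome would reflect better possession of medication or only fewer occasions on which to fail.

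**Working it through.** **The passages side by side (Objective 2, short term)**

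| Place in the protocol | Window | Measure |
| --- | --- | --- |
| 3.c, research question | 3 months | medication possession |
| 4.b, primary outcome | 4 months | all medications received |
| Table 3 | 4 months | all medications received |
| Table 4, planning rate | 3 months | all pickups made |

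Section 10.b ties the sample size to the short-term outcome, so a three-month rate is being used for a four-month endpoint.

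**The plan's sample size.** Inputs from section 10.b and Table 4: 12 clinics per arm, coefficient of variation k = 0.1, 80% power, alpha 0.05 (taken as two-sided), control rate 80%, difference 15 points (taken as 80% to 95%). The cluster formula for proportions is

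c = a + (1.96 + 0.84)² × [p0(1−p0)/m + p1(1−p1)/m + k²(p0² + p1²)] / (p0 − p1)²,

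with c = 12, and a = 1 for an unmatched or a = 2 for a matched design. Solving for m gives 12.9 (unmatched) or 15.7 (matched) per clinic. Multiplying by 1.2 gives 15.5 or 18.8. The stated 24 per clinic is not reproduced, but it is larger than these. How 24 was reached is a separate question; here only the margin matters.

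**Control rate at 4 months.** Assume that the 80% came from three monthly pickups with independent misses.

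- Per-pickup probability: q = 0.80^(1/3) = 0.928.
- Four pickups: 0.928⁴ = 0.743.
- Detecting 74.3% to 89.3% needs m = 15.9 (unmatched) or 18.9 (matched).
- Power at 24 per clinic: 87.7% or 84.5%.
- Power at 24/1.2 = 20 per clinic, if the whole 20% allowance is lost: 84.7% or 81.1%.

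**Difference produced by the schedule alone.** A club supplying every two to three months has between 4/3 ≈ 1.3 and 4/2 = 2 pickups due in 4 months, so take one or two. Use the same q in both arms (no difference in behaviour), monthly pickups in standard care, and every intervention-arm patient on the club schedule.

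| Window | Standard care | Two pickups | One pickup |
| --- | --- | --- | --- |
| 4 months | 0.928⁴ = 74.3% | 0.928² = 86.2% (+11.9) | 92.8% (+18.6) |
| 3 months | 0.928³ = 80.0% | 86.2% (+6.2) | 92.8% (+12.8) |

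**How far the assumptions drive this**

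- Uptake: at an assumed 50%, the 4-month figures halve to 0.5 × 11.9 = 6.0 and 0.5 × 18.6 = 9.3 points.
- Correlated misses: in the extreme, the same 20% of patients miss every pickup. The rate is then 80% for any number of pickups, and the difference is zero.
- Interval: if both arms collect at the same interval, the difference is zero.

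**The case against.** The two operative definitions, section 4.b and Table 3, agree on 4 months, and Table 4 only reports an outside clinic's experience as a planning input. That softens the contradiction but does not remove it. The research question still asks about another window and another quantity, and no reason is given.

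The scoring rule is not stated. Receiving all medications could mean supply covering the window, which would fit the research question, and the derivation may be left to an analysis plan that is not shown. This stands, and it is why the schedule effect is put conditionally. A later document cannot, however, settle which of the protocol's own windows is the primary one.

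The 12 to 19 points lie towards the upper end. They need monthly standard-care pickups, independent misses and full uptake. Section 4 itself expects that some eligible patients may not be enrolled in an intervention. This also stands.

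Fewer collections are part of how clubs are meant to work, and viral suppression at twelve months, the long-term primary outcome, does not depend on pickup counts. Both are true. Fewer occasions to fail may mean fewer gaps in supply, but a count of pickups kept cannot show whether it does.

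Three stronger readings are tempting and not supported:

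- **That delivery has the same bias.** Section 4.c gives no medication pickup interval, so the effect is only possible there.
- **That Objectives 2 and 3 must share a window.** They are analysed as separate cohorts, and a 4-month window has the merit of always containing a club date.
- **That the study is too small for this outcome.** The power figures above show otherwise.

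**Conclusion.** The contradiction holds on the text alone: 3 months against 4 months for a primary outcome, with three descriptions of what is measured and a planning rate that belongs to the shorter window.

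The schedule dependence is a conditional risk for clubs. If the outcome is scored as all scheduled pickups made, identical behaviour could produce anything from no difference to about 19 points over 4 months, against a planned effect of 15. The upper part of that range, 12 to 19 points, rests on assumptions that the protocol neither states nor excludes. The effect on sample size is small: under the same assumptions the 4-month control rate is about 74%, and 576 patients still give at least 80% power. The matter should be settled before analysis, because it decides what a positive club result would mean.

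**What to change.** 1. State one window for the club outcome in section 3.c, section 4.b, Table 3 and Table 4, long enough to contain a refill due date in both arms. It need not equal the Objective 3 window.
2. Define the outcome as medication possession on the same scale in both arms: for example, days covered over the fixed window, or medication in hand at its end.
3. Report all pickups made as a process measure, with the number of pickups due in each arm.
4. Restate the control rate for the chosen window. About 74% is the value at 4 months under the assumptions above.
5. State the medication pickup intervals expected under standard care and under delivery, so that a reader can judge whether the same issue arises for Objective 3.

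The cost is wording and one derived variable. Table 2 and the field list in section 9.b already include medication pickup dates and next scheduled visit dates, so no new fields, sites or patients are needed. There are two drawbacks. Days supplied must be inferred from the next scheduled date where they are not recorded. A longer supply dispensed at entry can also raise days covered by itself, so possession at the end of the window should be shown alongside it.

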Each of the interventions, while implemented as a package of services, will be delivered to a unique population within each clinic: patients newly eligible for ART, patients stable on ART, patients with poor adherence, and patients lost from care. (The exception to this is patients who are stable on ART and could be provided with either decentralized medication delivery or adherence clubs, but not both.) This will allow us to estimate the effect of each intervention individually, in the context of implementation of the overall minimum package. During the early stages of implementation of the Adherence Guidelines it is possible that eligible patients at intervention sites might not all be enrolled in an intervention they are eligible for. In order to ensure that this evaluation does not by chance exclude eligible patients who are exposed to the interventions, enrolment at intervention sites will include not only those eligible for the intervention but also eligible patients who receive the intervention.

The following five interventions will be evaluated under this protocol. Each is described in detail in the National Adherence Guidelines[11]. (Note: Additional details about primary and secondary outcomes, eligibility criteria, sample size, and data sources are included in later sections of this protocol.)

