- *Setting*. Both sites in each pair should draw from the same type of community: urban; informal settlement; or rural.
- *Location*. Pairs should be located relatively nearby one another, to facilitate data collection and increase similarity of the catchment populations.

- *HIV viral suppression*. The clinics in the pair should have ART patient viral suppression rates within 10% percent of one another (if data available).

Letters indicating Provincial and District Department of Health authorization to work at each study site have been obtained and are attached. The final number of clinics selected remains at 24 clusters.

In each pair, one clinic will randomly be assigned to receive early implementation of the minimum package of interventions, while the other will continue to provide standard of care. Randomization will be done through a random number generator in Microsoft Excel with a 1:1 ratio of allocation to intervention and control clusters.

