## **b. Inclusion and Exclusion Criteria**

For Objectives 1-5 and Objective 8, we will enroll a specific cohort of patients. These will be numbered in accordance with the objective number for Objectives 1-5; for Objective 8, the cohort will be called the “TBHD cohort”, in reference to tuberculosis, hypertension, and diabetes. This TBHD cohort will be made up of patients who have been screened for TBHD (50%) and patients who are newly diagnosed with TB, hypertension or diabetes (50%). For all cohorts, inclusion and exclusion criteria are as shown below. For Objectives 1-5, these criteria follow the December 2014 national guidelines for HIV care and ART[10] and November 2015 National Adherence Guidelines for Chronic Disease (HIV, TB and NCDs) [11].

*Cohorts 1-5 and TBHD cohort inclusion criteria*

- ≥ 18 years old
- Meet the inclusion criteria for one or more of Cohorts 1-8

*Cohorts 1-5 and TBHD cohort exclusion criteria*

- Not resident in the facility’s catchment area
- Recorded intention to transfer care to a different facility within 12 months
- Pregnant and eligible for PMTCT

*Objective 1/Cohort 1 inclusion criteria (Patients newly eligible for ART—fast track treatment initiation)*

- Determined to be eligible to start ART under prevailing national guidelines (CD4 count < 500, WHO Stage 3 or 4 condition, TB, cryptococcal meningitis)

*Objectives 2 and 3/Cohorts 2 and 3 inclusion criteria (Patients stable on ART—adherence clubs or decentralized medication delivery)*

- On same ART treatment regimen for at least 12 months
- Most recent viral load taken in past 6 months
- Two consecutive viral loads undetectable (<400 copies/ml^3^)

*Objective 4/Cohort 4 inclusion criteria (Patients on ART with poor adherence—enhanced adherence counseling)*

- On first line ART for at least 6 months
- Poor adherence as indicated by an elevated viral load (>400 copies/ml^3^)

*Objective 5/Cohort 5 inclusion criteria (Patients lost from ART programs—early patient tracing)*

- Initiated ART
- Fail to return for a scheduled appointment within 5 to 90 days from their appointment date

*Objective 8/TBHD cohort inclusion criteria (Tuberculosis, hypertension, and diabetes patients)*

- Screened for or diagnosed with for TB or hypertension within the last month, or diabetes within last 6 months

*Objective 8/TBHD cohort exclusion criteria (Tuberculosis, hypertension, and diabetes patients)*

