## **d. Data Entry and Storage**

During the enrollment period, which we anticipate to last for approximately six months, patients will be identified and enrolled from TIER.Net (Cohorts 1-5) and site records (TBHD cohort) consecutively until sample size targets are met. “Enrollment” will consist only of reviewing site records to select patients who have become newly eligible for the study in the previous interval; there will be no contact with patients for study purposes.

As explained above, the study will not generate any new data beyond what is called for by existing guidelines and procedures. To allow a valid evaluation, we will make efforts to ensure that the data the clinics are supposed to record are collected and documented completely and promptly. Study staff will visit the sites regularly to obtain electronic data sets, capture paper records and registers on electronic case report forms on dedicated tablets, and review data quality. If needed, study staff will assist the sites to complete all routine forms and records and enter them into a database. Once initial data collection systems are in place, we anticipate visiting each site at least every 10 days to collect data sets, review procedures, and respond to data queries from the previous visit. In order to ensure a secure transmission, the electronic data sets obtained from the clinic will be transferred from the study site via a dedicated secure VPN onto protected drives at the local office.

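### Sections 4b and 4c let a clinician's confirmation of stability qualify a patient for Cohorts 2 and 3, section 8b does not, and nothing says which entry rule governs.

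*Protocol*

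**What the plan says.** The eligibility rows in Protocol sections 4b (Adherence Clubs) and 4c (Decentralized Medication Delivery) read alike. Each gives a regimen criterion and two viral-load criteria, then adds an alternative: "OR where a clinician confirms eligibility as a stable patient".

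Section 8b (Inclusion and Exclusion Criteria) gives three criteria for Cohorts 2 and 3 and no alternative:
- a stable regimen: "On same ART treatment regimen for at least 12 months"
- a latest viral load that is no more than six months old
- documented suppression: "Two consecutive viral loads undetectable (<400 copies/ml^3"

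Four other places bear on how the rule would work:
- **Section 8a:** one clinic in each pair receives the package, "while the other will continue to provide standard of care".
- **Section 9d:** "patients will be identified and enrolled from TIER.Net (Cohorts 1-5) and site records (TBHD cohort) consecutively until sample size targets are met".
- **Section 9c:** a patient's enrolment starts on the date eligibility is determined.
- **Section 10c:** the stated response to imbalance is to adjust for covariates on which an imbalance is detected.

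**The concern.** Two entry rules for one cohort define two populations. A patient without two documented undetectable loads, or without a recent one, is outside Cohorts 2 and 3 under section 8b but may be inside them under 4b and 4c. This affects two of the five effectiveness comparisons.

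The clinician route is also harder to apply evenly than a rule read from laboratory and dispensing dates. The protocol does not say what the confirmation rests on, how it is recorded, or whether it is sought in comparison clinics. Clinics are randomised before patients are picked from records, so any difference between arms in the use of this route is selection after randomisation.

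Both primary outcomes for these cohorts (all medications received in the short term, viral suppression at twelve months) plausibly depend on adherence and suppression at entry, which is what a judgement of stability concerns. If some patients enter without documented suppression, the twelve-month outcome means maintained suppression for some and newly achieved suppression for others. The outcome clock could also start on a clinician's decision date for some patients and on a laboratory date for others.

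**Working it through.** **Step 1: the two rules side by side.**

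| Entry condition, Cohorts 2 and 3 | 4b and 4c | 8b |
| --- | --- | --- |
| Same regimen for at least 12 months | yes | yes |
| Latest viral load within 6 months | yes | yes |
| Two consecutive undetectable loads | yes | yes |
| Clinician confirmation as an alternative | yes | absent |

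The rules agree for patients who meet all three fixed criteria and can disagree for everyone else.

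**Step 2: does the text settle which governs?** The introduction to section 4 points to later sections for further detail on eligibility, which favours 8b. It does not say that 8b overrides section 4, and an added detail is not the same as the removal of an alternative. The question stays open.

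**Step 3: can the clinician route be ascertained alike in both arms?** The field list in section 9b includes dates of eligibility for interventions, Adherence Plan fields where entry is feasible, changes to first-line regimens with dates, and all viral loads with dates. It has no dedicated field for clinician confirmation or route of entry. The fixed criteria can therefore largely be rebuilt from planned data. The clinician's judgement and its grounds cannot be relied on to be there.

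**Step 4: possible size.** The plan gives no figure to reproduce. Let q be the share of one arm's cohort that enters only by the clinician route, with almost none in the other arm, and d the difference in underlying outcome risk between those patients and the rest. Both are assumptions.

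Shift in the arm contrast = q × d
- q = 20%, d = 10 points: 0.20 × 10 = 2.0 points
- q = 30%, d = 15 points: 0.30 × 15 = 4.5 points
- Wider range, q from 10% to 30% and d from 5 to 20 points: 0.10 × 5 = 0.5 to 0.30 × 20 = 6.0 points

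**Step 5: what such a shift would do to the test.** Inputs from section 10b and Table 4: 12 clusters per arm, 24 patients per clinic, coefficient of variation 0.1, alpha 0.05, control rate 80%, target difference 15 points (80% v 95%). A two-sided test is assumed, with the Hayes-Bennett unmatched variance:

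Var = { [p1(1−p1) + p2(1−p2)] / 24 + 0.1² × (p1² + p2²) } / c

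Here c is 12, or 11 with the usual one-cluster allowance.

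Example with no true effect, p1 = 0.80, a 4.5-point shift (p2 = 0.845) and c = 12: the standard error is 0.0462, 0.045 / 0.0462 = 0.97, and the two-sided rejection probability is about 16%.

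| Shift | Rejection with no true effect | Power for 80% v 95% if the shift is against the intervention |
| --- | --- | --- |
| 0 | 5% | 89–92% |
| 2.0 points | about 7% | 79–82% |
| 4.5 points | 15–16% | 60–64% |

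The ranges are c = 11 and c = 12. The calculation ignores matching and uses the pickup outcome only. It shows scale and is not an estimate of actual bias.

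**The case against.** The strongest reply is that 8b governs. It is the section headed as inclusion and exclusion criteria, it defines cohorts by number, and section 4 defers to later sections for detail. Sections 4b and 4c would then summarise who may be offered the service, and the clinician route would admit nobody to the evaluation. This is a reasonable reading, and it is why bias is not demonstrated. It still leaves 4b and 4c wrong as written.

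A reader might go further and infer that intervention clinics will enrol clinician-selected patients while comparison clinics enrol only patients meeting the viral-load rule. The documents do not support that. The clause is worded alike for both arms. Nothing says that clinicians at comparison sites do not confirm stability, and section 8a expects most clinics to provide some adherence support already. Placing a patient in a club or delivery scheme is a natural occasion for certifying stability, but that is inference. The explicitly arm-specific rule is a separate one in section 4: "enrolment at intervention sites will include not only those eligible for the intervention but also eligible patients who receive the intervention". The present point does not depend on it, although a looser meaning of eligible would also loosen that rule.

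Three further replies have partial force:
- If confirmation is recorded nowhere, record reviewers could hardly enrol on it in either arm. That lowers the likely size but does not settle the rule.
- The clause may be meant for patients with incomplete records and not as an override. Section 4b refers to a guideline procedure that is not at hand, so this cannot be decided.
- Section 10c provides for adjustment. It covers only imbalances that are detected, and cannot fully remove selection on an unrecorded judgement.

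**Conclusion.** The textual conflict is certain: sections 4b and 4c contain an entry route that 8b lacks, and no text ranks them. Confidence in this is high.

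That the conflict could bias the Cohort 2 and 3 comparisons is a possibility, held with moderate confidence. It requires that the clinician route is actually used for cohort entry, that its use differs by arm, and that the patients concerned differ in underlying outcome. The illustrative 2 to 4.5 points rests wholly on assumed q and d. The direction is unknown and could differ between outcomes: upward for pickups if clinicians choose adherent patients, downward for suppression if those patients lack two undetectable loads. A larger sample would not remove such a bias.

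This should be fixed. It does not show that the comparisons are already biased.

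**What to change.** Reconcile sections 4b, 4c and 8b to one rule for entry to the evaluation cohorts, applied identically in both arms from records.

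- **Primary comparison:** use the three section 8b criteria, derived from the regimen and viral-load dates already to be collected.
- **Eligibility date:** define it the same way in both arms, for example as the first date in the enrolment period on which the records satisfy all three criteria.
- **Clinician-confirmed patients:** flag anyone entered only on a clinician's confirmation, and report them descriptively or in a sensitivity analysis that adds them back.
- **Scope:** state that the rule governs entry to the evaluation only and not whom clinics serve.

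The cost is one wording amendment and a filter on planned data. Patients without the required documented viral loads would not count towards the 24 per clinic, so enrolment may be slightly slower. The evaluated population becomes somewhat narrower than the one served, which matters because section 3c describes the impacts as those of the interventions as implemented. The sensitivity analysis keeps that wider group in view.
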